## **8. Study end-points**

### **8.1 Primary end-points**

(1) Time from birth to the last meconium evacuation

This trial will use the standard infant meconium evacuation form. Nursing personnel will be trained to correctly identify the infant's meconium, transitional meconium, and normal feces. Detailed information on the evacuation and characteristics of each meconium will be recorded, and questionable meconium photos will be recorded and discussed in group meetings.

(2) Time to achieve total enteral feeding in super premature infants and preterm infants (when the infant tolerates a volume of 180 ml/kg/day for at least 24 h or undergoes weight gain greater than 20-25 g/d in 24 h)

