## **7.2 Feeding schedule**

The same feeding and parenteral nutrition procedures will be used for premature infants in control and intervention groups. The total daily calories of enteral and parenteral nutrition will be 110–135 kcal/kg. Premature infants will be fed starting at 24 mL/kg birthweight per day. Furthermore, feedings will be advanced every 24 hours by 20 mL/kg birthweight per day. When the amount of enteral feeding reaches 120 mL/kg per day, parenteral nutrition will be stopped. We defined full enteral feeding as tolerance of enteral feeding volumes of 180 mL/kg/day within 24 hours and a weight gain greater than 20–25 g/d within 24 hours. Human milk feeding will be encouraged. If the amount of breast milk is insufficient to meet the nutritional needs of premature infants, mixed feeding (artificial and breast milks) will be adopted. We will use disposable bottles for feeding to calculate the volume of feeding and use nasogastric feeding for premature babies with poor sucking ability. Feeding will be stopped if feeding intolerance occurs, such as when a gastric residual volume occurs that is more than half of the feeding volume, an abdominal circumference that is increased by 2 cm more than before the previous feeding, or with the occurrence of an intestinal dynamic anomaly.

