#### **14.2 Analysis of Primary Outcomes**

The two primary outcomes include the time to achieve complete meconium evacuation and the time to complete enteral feeding. Outcomes are presented as median (Q1-Q3). The outcomes will be analyzed using an independent sample t-test or Mann–Whitney test. Meanwhile, a multiple linear regression model will be used to analyze the factors affecting primary outcomes, including gender, birth weight, history of a mother's disease, etc. For outcome differences between the treatment and control arms, the median difference and 95% confidence interval (CI) will be assessed using the Mann–Whitney U test and the Hodges–Lehmann method. The time to achieve complete meconium evacuation and full enteral feeding will be analyzed using Kaplan–Meier curves and log-rank tests. In the Kaplan–Meier analysis, the computation of the median time holds significant methodological importance.

Precisely, the median time to accomplish complete meconium evacuation and full enteral feeding are ascertained as the time point at which 50% of the study participants reach these predefined endpoints.

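### The second primary endpoint, full enteral feeding, has two incompatible definitions: section 7.2 joins its criteria with *and*, section 8.1 with *or*, and the two can date the same infant's event several days apart

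*Protocol*

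**What the plan says.** Section 7.2 (Feeding schedule) gives this definition of the feeding milestone: "tolerance of enteral feeding volumes of 180 mL/kg/day within 24 hours and a weight gain greater than 20–25 g/d within 24 hours". Both conditions must hold.

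Section 8.1 (Primary end-points) gives the second primary endpoint as the time to total enteral feeding, reached when the infant "tolerates a volume of 180 ml/kg/day for at least 24 h or undergoes weight gain greater than 20-25 g/d in 24 h". Either condition is enough.

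Section 7.2 also sets the pace of feeding: "Premature infants will be fed starting at 24 mL/kg birthweight per day", and "feedings will be advanced every 24 hours by 20 mL/kg birthweight per day". On parenteral support it says "The total daily calories of enteral and parenteral nutrition will be 110–135 kcal/kg" and "When the amount of enteral feeding reaches 120 mL/kg per day, parenteral nutrition will be stopped".

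Section 14.2 names the endpoint as primary ("The two primary outcomes include the time to achieve complete meconium evacuation and the time to complete enteral feeding") and lists the tests, but gives no definition that would settle the conflict. The objectives in section 2 and the data items in section 9.2 do not settle it either.

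**The concern.** A time-to-event endpoint needs one rule that turns an infant's record into one date. Here two sections give different rules for a primary endpoint. Two people who each follow the protocol could date the same infant differently, and every analysis in 14.2 (rank test, Hodges–Lehmann difference, Kaplan–Meier, log-rank) would inherit the difference.

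The rules also do not measure the same thing. In 8.1 the weight criterion carries no volume condition, so it can be satisfied by an infant receiving little enteral feed, with calories still coming partly by the parenteral route. In 7.2 an infant who tolerates the full volume is not an event until the weight condition is met as well.

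Two smaller ambiguities add to this. One section speaks of a volume within 24 hours, the other of at least 24 hours. And a gain above 20–25 g/d is not a threshold: a gain of 22 g passes if the limit is 20 and fails if it is 25.

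If the choice between the rules is left until outcome data are available, the primary result depends on a decision that was not prespecified.

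**Working it through.** **Inputs, all from section 7.2.** Starting volume 24 mL/kg/day; advance 20 mL/kg/day every 24 hours; parenteral nutrition stops at 120 mL/kg/day; volume criterion for the endpoint 180 mL/kg/day. The protocol states no expected number of days to full feeding, so there is no figure of its own to reproduce.

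**Volume on feeding day k**, with uninterrupted advances from the first feed:

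V(k) = 24 + 20 × (k − 1)

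| Feeding day | 1 | 2 | 3 | 4 | 5 | 6 | 7 | 8 | 9 |
|---|---|---|---|---|---|---|---|---|---|
| mL/kg/day | 24 | 44 | 64 | 84 | 104 | 124 | 144 | 164 | 184 |
| Parenteral nutrition | on | on | on | on | on | off | off | off | off |
| Days before 180 is reached | 8 | 7 | 6 | 5 | 4 | 3 | 2 | 1 | 0 |

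- To reach 120: (120 − 24)/20 = 4.8, so 5 advances, feeding day 6.
- To reach 180: (180 − 24)/20 = 7.8, so 8 advances, feeding day 9.

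**Earliest event under each rule.** Let T_vol be the day the volume criterion is met and T_wt the first day the weight criterion is met.

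- *And* (7.2): the event cannot come before the later of T_vol and T_wt. Since T_vol is at least day 9, neither can the event. The same bound holds for volume alone.
- *Or* (8.1): the event is the earlier of T_vol and T_wt. T_wt has no volume condition, so it can fall at any weighing that shows a qualifying gain.

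The *or* date is thus never later than the *and* date for the same infant. A qualifying gain on feeding days 1 to 5, with parenteral nutrition running, precedes the earliest day at 180 by 9 − 5 = 4 to 9 − 1 = 8 days. A gain on days 6 to 8 precedes it by 3 to 1 days.

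**Direction of the simplifications.** Section 7.2 stops feeds for intolerance, which pushes day 9 later and widens the gap. The days count from the first feed. Section 8.1 states no time origin for this endpoint, but a shift of origin moves both dates equally and leaves the gap unchanged.

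**The case against.** The best defence is that 7.2 is the express definition and that the *or* in 8.1 is a drafting slip. The 8.1 criteria stand in parentheses after the words total enteral feeding, and calling an infant at 44 mL/kg/day on parenteral nutrition fully fed contradicts the endpoint's own name. That is plausible, and the two duration phrases may be loose wording for the same period. But 8.1 is where the primary endpoint is specified, its text permits the literal reading, and no statement gives 7.2 precedence. The early event stands as a possibility under the wording, not as a forecast.

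Stronger readings are tempting, and the protocol does not support them:

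- **That the *or* rule would swamp a treatment effect.** The protocol gives no early weight changes, and section 11 sizes the trial on meconium evacuation only, so neither the frequency of early events nor the resulting dilution can be calculated. To illustrate, assume seven independent days (feeding days 2 to 8) and normally distributed daily gains. The chance of at least one gain above 25 g is 1 − Φ((25 − mean)/SD)^7. With mean −10 g and SD 10 g this is 1 − Φ(3.5)^7, about 0.2%. With mean 10 g and SD 20 g it is 1 − Φ(0.75)^7, about 83%. A spread that wide is no estimate.
- **That the *and* rule keeps the smallest infants from reaching the endpoint.** This needs body weights and growth rates that the protocol does not give.
- **That the open-label design makes the ambiguity a source of biased assessment.** Section 6 blinds outcome assessors and data analysts. That weakens the argument, although a blinded assessor still needs one rule.
- **That volume alone is the right definition.** It appears in neither section, and the choice is clinical.

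**Conclusion.** The point holds as an internal contradiction on a primary endpoint. It is wrong as written, not a detail left to a later analysis plan, because the protocol itself states two incompatible rules. On its own schedule the *and* rule cannot be met before feeding day 9, while the literal *or* rule can be met 4 to 8 days before 180 mL/kg/day is reachable, with parenteral nutrition still running. The day counts assume uninterrupted advances from the first feed; interruptions enlarge the gap.

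The size of any effect on the treatment comparison is unknown and should not be asserted. The sample size in section 11 rests on the other primary endpoint and is not affected.

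**What to change.** Reconcile 7.2 and 8.1 into one definition, repeated word for word in both and used in 14.2. It should have:

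- one connective;
- one duration;
- if weight gain is kept, one stated cut-off in place of the range.

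Settle it before outcome data are seen, and analyse the alternative wording as a sensitivity analysis where the data allow. The sponsor decides which definition is clinically right. The feeding schedule is not touched.

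Also confirm that daily enteral volume and daily weight are recorded. Section 9.2 lists body weight without a frequency and does not list daily feed volume. Section 7.2 mentions calculating feed volumes and section 12.8 mentions daily follow-up, so the data probably exist, but the protocol does not guarantee it. Section 12.8 also ties follow-up to reaching the endpoints, so it should be clear that these records continue until the event under either wording can be dated.

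The cost is a wording amendment and, if needed, two lines on the data collection form.

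### The second primary end-point joins its two criteria with 'and' in section 7.2 but with 'or' in section 8.1, so one infant's record can give two different event times

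*Protocol*

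**What the plan says.** Objective 2 (Protocol, section 2) is whether breast milk shortens the time to full enteral feeding, and section 8.1 makes that time the second of two primary end-points. The protocol defines the event twice.

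- Section 8.1: reached when the infant "tolerates a volume of 180 ml/kg/day for at least 24 h or undergoes weight gain greater than" 20–25 g in a day.
- Section 7.2: "tolerance of enteral feeding volumes of 180 mL/kg/day within 24 hours and a weight gain greater than 20–25 g/d within 24 hours".

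Section 9.2 (data collection) and section 14.2 (primary analysis) use the end-point without defining it.

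Section 7.2 also fixes the feeding schedule: "Premature infants will be fed starting at 24 mL/kg birthweight per day", and "feedings will be advanced every 24 hours by 20 mL/kg birthweight per day". On parenteral nutrition it says: "When the amount of enteral feeding reaches 120 mL/kg per day, parenteral nutrition will be stopped". The calorie target covers both routes: "The total daily calories of enteral and parenteral nutrition will be 110–135 kcal/kg".

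**The concern.** 'And' and 'or' describe different events. Under 'or', the first criterion to be met stops the clock. Under 'and', the clock runs until both are met. The two agree only if both criteria are first met on the same day.

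The 'or' version also raises a validity problem. Weight gain reflects total intake, and early in the schedule part of that intake is parenteral. A day's weight rise can then score full enteral feeding at a low enteral volume, which is not what objective 2 asks about.

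At stake is one of the two primary comparisons. Section 14.2 applies the t-test or Mann–Whitney test, the Hodges–Lehmann estimate, regression, and Kaplan–Meier with log-rank to this time, and all of them inherit whichever definition is used. The trial is open-label, with only assessors and analysts blinded (section 6). While both definitions stand, either could be presented afterwards as the prespecified one, and a reader could not tell.

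**Working it through.** **Plan's own figure.** There is none to reproduce. Section 11 sizes the trial on meconium evacuation only and states no expected time to full enteral feeding.

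**Inputs, all from section 7.2:** starting volume 24 mL/kg/day; advance of 20 mL/kg/day every 24 hours; parenteral nutrition stopped at 120 mL/kg/day enteral; volume criterion 180 mL/kg/day. The first day of qualifying weight gain, W, is not given anywhere and is varied below.

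**Step 1: schedule without interruption.** Volume on feeding day k = 24 + 20(k − 1).

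- Days 1 to 5: 24, 44, 64, 84, 104 mL/kg/day. All are below 120, so parenteral nutrition is running.
- (120 − 24)/20 = 4.8, so five advances are needed: day 6, at 124 mL/kg/day.
- (180 − 24)/20 = 7.8, so eight advances are needed: day 9, at 184 mL/kg/day.

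**Step 2: event day under each wording.** Each criterion is assigned to the 24-hour block in which it is met.

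- 'Or' (section 8.1): event day = min(W, 9).
- 'And' (section 7.2): event day ≥ max(W, 9). It is a lower bound because an early qualifying gain need not recur on the day the volume is reached.
- Gap ≥ max(W, 9) − min(W, 9) = |9 − W|.

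| W (feeding day) | 'Or' scores on | Enteral volume that day (mL/kg/day) | Parenteral nutrition | 'And' scores no earlier than | Minimum gap (days) |
|---|---|---|---|---|---|
| 1 | day 1 | 24 | running | day 9 | 8 |
| 2 | day 2 | 44 | running | day 9 | 7 |
| 3 | day 3 | 64 | running | day 9 | 6 |
| 5 | day 5 | 104 | running | day 9 | 4 |
| 9 | day 9 | 184 | stopped | day 9 | 0 |
| 12 | day 9 | 184 | stopped | day 12 | 3 |

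**Step 3: interruptions.** Section 7.2 stops feeding for intolerance, so day 9 is the earliest possible day. If the volume is first reached on a later day V, the same argument gives a gap of at least |V − W|, with no fixed upper limit.

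**Step 4: what 'or' can score.** For W on days 1 to 5 the end-point is recorded at 24–104 mL/kg/day with parenteral nutrition running. For W on days 6 to 8 parenteral nutrition has stopped, but the volume (124, 144, 164 mL/kg/day) is still below 180.

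Both sections state the weight threshold as a range (20–25 g/d). That is common to both and changes none of the steps above.

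**The case against.** **It is only a drafting slip.** That may be so, but the protocol does not show which word is the slip. A separate statistical analysis plan, not at hand, might choose one version, but it would have to overrule one section of the protocol.

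**The gap may be small.** This is correct as a possibility: if weight gain first qualifies on day 9 of an uninterrupted schedule, the minimum gap is zero.

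**The two time wordings (within 24 hours; for at least 24 hours) are loose drafting.** This stands. On their own they do not show two different events; the case rests on 'and' against 'or'.

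**Stronger readings that the protocol does not support.**

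- A reader might infer that the definitions score infants about a week apart. Even a minimum gap of 6–8 days needs W on feeding days 1–3 (or a late gain or delayed feeds), and the protocol gives no growth curve, weighing error or interruption rate.
- A reader might infer that 'or' events are mostly weight changes supported by parenteral nutrition. One simulation on assumed inputs (mean birth weight 1.1 kg, gain 15 g/kg/day after day 5, no feed advance on 25% of days, weighing error SD 5, 10, 15 or 20 g) put the share of 'or' events below 120 mL/kg/day at 20, 36, 46 and 54%: a minority in three of four settings.
- A reader might infer that 'or' destroys power. Varying assumed birth weight (0.8–1.3 kg), gain (10–20 g/kg/day) and weighing error (SD 5–20 g) moved the share of 'or' events below 180 mL/kg/day from 11% to 100%. The treatment difference kept under 'or' ran from about 0 to 1.1 days, against about 1.2 days by volume. The inputs decide the answer, so these figures are illustrative only.
- A reader might infer that volume alone is the intended end-point. Both sections include weight gain, so that would be a third definition.

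**Conclusion.** The contradiction is explicit, unresolved elsewhere in the protocol, and falls on a primary end-point. It must be settled, because at present the end-point has no single value per infant.

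The size that can be defended is the bound |9 − W| days on the uninterrupted schedule: from 0 to 8 days if weight gain first qualifies by day 9, and growing again after that. It rests only on the schedule in section 7.2 and on W, which is unknown. That 'or' can score an infant still on parenteral nutrition as fully enterally fed follows from the text without further assumption; how often it would happen does not. No typical gap, share of events or power figure can be derived from the protocol.

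**What to change.** Reconcile sections 7.2 and 8.1 into one outcome definition, worded identically in both places with a single 24-hour wording, and fix it before any data by arm are seen. The definition should not let weight gain alone score the event; for example, replace the 'or' of section 8.1 with the 'and' of section 7.2. This concerns how the outcome is scored. It changes no infant's feeding, and no view is taken on which volume or gain is clinically right.

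The cost is a one-sentence amendment and a matching registry entry. Feed volumes, body weight and parenteral nutrition are already recorded under sections 7.2 and 9.2. The small downside is that the event falls later than under 'or', so a few more infants may be censored before reaching it.

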### **8.2 Secondary end-points**

(1) Stage II or III necrotizing enterocolitis (NEC, Bell standard)

(2) Hospitalization days

(3) Body weight at discharge

(4) Duration of total parenteral nutrition

(5) Cholestasis(Serum binding bilirubin concentration > 1.0 mg/dL (17.1 mmol/L)

Serum total bilirubin < 5.0 mg/dL (85.5 mmol/L) or >20%

Total bilirubin concentration >5.0 mg/dL (85.5 mmol/L), measured 2 weeks after birth in two groups

(6) Any adverse events reported: nosocomial infection, nosocomial death, retinopathy of prematurity (ROP, any stage), chronic lung disease (CLD), requirement of ventilatory support or oxygen after a corrected gestational age of 36 weeks, intraventricular hemorrhage (IVH, grade 2 and above), bronchopulmonary dysplasia (BPD), late-onset sepsis (LOS), diarrhea, colon perforation, malabsorption, rectal bleeding, and rectal trauma.

## **9. Data collection**

The research data will be collected by trained researchers using standardized questionnaires and measurements to ensure accuracy. At baseline, the following information regarding premature infants and their mothers will be collected: gestational age, birth weight, demographic information, history of disease, and medications used during pregnancy. The following major aspects of outcome information will be collected during the follow-up: meconium evacuation, feeding, laboratory tests, and adverse events.

## **9.1 Baseline demographic information**

(1) Mother's information: general information (name, age, date of birth, ethnicity, education level, ID number, home address, and contact information), medical history (pregnancy-induced hypertension syndrome and gestational diabetes), use of medicine during pregnancy, infant delivery method, and maternity.

(2) Infant's information: gestational age, sex, birth weight (g), starting time of enteral feeding within 48 hours after birth, method of enteral feeding (breast milk only/breast milk formula mix/formula only), and Apgar score (1 min, 5min).

## **9.2 Follow-up data collection**

(1) End-point information: body weight (g), meconium evacuation time (h), fecal type, abnormal traits and color; time to achieve total enteral feeding (h), duration of total parenteral nutrition (h), feeding tolerance (residual milk volume, nature of the residual liquid, abdominal circumference before the two feedings, bowel sounds, and intestinal motility conditions), route and method (breast milk only/breast milk formula mixed/formula milk powder only) of feeding, type of formula, C-reactive protein measurements, blood culture results, blood oxygen measurements, Whether to perform phototherapy, serum bilirubin levels, neonatal intensive care unit time, and NEC.

(2) Adverse events: nosocomial infection, in-hospital death, ROP, CLD, IVH, BPD, LOS, diarrhea, colon perforation, malabsorption, rectal bleeding, and rectal trauma.

## **10. Data management and quality control**

All super premature and preterm infants will be uniquely coded (ID) according to the same rules. After the data are checked by the quality control commissioner, the Epidata database will be used for double entry. Logical verification and positioning and modification will be performed. The data will be managed throughout the process. The locked database will be used for analysis after the accuracy is confirmed.

### **10.1 Baseline data quality control**

- a. Carefully design and develop the questionnaire.
- b. Consistently train investigators.
- c. Implement consistent standards for all operations.

### **10.2 Follow-up data quality control**

- a. The infants will be monitored by dedicated nurses, and the treatment will be performed by a dedicated nurse.
- b. Recorded events will be collected through consistent standards.
- c. Integrated data entry and input verification will be performed.

### **10.3 Missing data**

The relevant researcher will contact the premature infant's guardian by telephone or check electronic medical records to supplement missing baseline and follow-up data. If no reply is received from the guardian or missing data cannot be supplied, the missing data will be processed using different methods based on the mechanism of the missing data. For example, mean value imputation and last observation carried forward will be used to supplement the data. Furthermore, we will conduct a sensitivity analysis to evaluate the robustness of trial results: When we analyze primary outcomes, we will conduct a comparative analysis of complete (ignoring the missing data) and incomplete (no missing data) cases.

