## **11. Sample size and statistical power estimation**

The sample size estimate is based on our pilot study; the time of complete meconium evacuation was 1.4 days, 1.2 days, and 1.2 days earlier in the breast milk enema group than in the saline enema group at  $23 \text{ w} \leq \text{gestational age} < 28 \text{ w}$ ,  $28 \text{ w} \leq$

gestational age < 29 w, and 29 w  $\leq$  gestational age < 30 w, respectively. Given that  $\alpha = 0.05$ ,  $\beta = 0.2$ , standard deviation (SD) = 2, sampling ratio = 1 and taking a 20% drop rate into account, the required total sample size is 78, 108, and 108 premature infants in each gestational age, respectively. A website was used to calculate the sample size (<http://powerandsamplesize.com/Calculators/>).

| Gestational age               | Difference | $\alpha$ | $\beta$ | SD | Sample size | Loss of follow-up | Final sample size |
|-------------------------------|------------|----------|---------|----|-------------|-------------------|-------------------|
| 23W $\leq$ Gastinal age < 28W | 1.4d       | 0.05     | 0.2     | 2  | 64          | 20%               | 78                |
| 28W $\leq$ Gastinal age < 29W | 1.2d       | 0.05     | 0.2     | 2  | 88          | 20%               | 108               |
| 29W $\leq$ Gastinal age < 30W | 1.2d       | 0.05     | 0.2     | 2  | 88          | 20%               | 108               |

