## 15. Discussion

Due to the large number of premature infants being born worldwide, countries are facing an enormous medical burden. Feeding is a significant challenge for premature infants and establishing full enteral feeding is an important goal in their care. Earlier full enteral feeding is associated with fewer failures of postpartum growth. Unfortunately, any delay in meconium excretion is related to a delay in transition to full enteral feeding. Compared with term infants, many premature infants pass the first meconium only after considerable delay. Times for the evacuation of the first and last meconium is critical for gastrointestinal function and feeding tolerance. If meconium evacuation can be expedited through the use of an effective enema, this may lead to a faster transition to full enteral feeding and a decreased reliance on intravenous nutrition. However, the available evidence is inconclusive. In contrast to other enemas, the amount of magnesium salts in breast milk is high and relatively stable, which can promote gastrointestinal peristalsis and help meconium evacuation[21,22]. In addition, breast milk can reduce the risk of enterovirus infection and balance the intestinal flora of premature infants[23,24]. Therefore, the trial will collect all participants' data to determine whether this trial has potential clinical significance and can provide reliable evidence for clinical intervention. The results may yield a new, safe, inexpensive, and easy-to-use intervention to effectively evacuate meconium in preterm infants.

To the best of our knowledge, the major strength of this randomized controlled trial is to evaluate, for the first time, the effectiveness of a breast milk enema in promoting complete meconium evacuation and reach full enteral feeding among preterm and extremely preterm infants. Consequently, the results will provide critical information regarding a new enema to effectively evacuate meconium in preterm infants.

The study protocol has several limitations. First, some infants achieving complete meconium evacuation may withdraw before observing the time to reach full enteral feeding. We will further analyze and design a more comprehensive investigation

482 based on this study. Second, this trial is a single-center clinical trial. Therefore, the  
483 representativeness of the participants is limited to some extent. Finally, some mothers  
484 may be unable to produce enough breast milk in early postpartum, which may slow  

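### Section 10.3 names mean imputation and last observation carried forward for missing follow-up data and does not exempt the two primary event times, which are right-censored when an infant is lost

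*Protocol*

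**What the plan says.** Protocol section 10.3 first has staff telephone the guardian or search the records "to supplement missing baseline and follow-up data". Where that fails, "the missing data will be processed using different methods based on the mechanism of the missing data". The examples that follow are that "mean value imputation and last observation carried forward will be used to supplement the data". No other method is named, and no method is tied to a particular mechanism. For the primary outcomes, the section adds a sensitivity analysis that sets results without the missing cases beside results in which nothing is missing. The labels there are hard to follow; I read this as complete cases against imputed data.

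Section 9.2 lists both primary event times, in hours, among the follow-up end-point data. Section 14.1 commits to intention-to-treat and per-protocol analyses. Section 14.2 compares the primary outcomes by t-test or Mann–Whitney test, with a Hodges–Lehmann interval. It then adds: "The time to achieve complete meconium evacuation and full enteral feeding will be analyzed using" Kaplan–Meier curves and log-rank tests.

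On loss, section 11 works with "standard deviation (SD) = 2, sampling ratio = 1 and taking a 20% drop rate into account". Section 15 concedes that "some infants achieving complete meconium evacuation may withdraw before observing the time to reach full enteral feeding".

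**The concern.** Both primary outcomes are times to a once-only event. When an infant leaves before the event, the data say only that the true time is later than the last time the infant was seen event-free. A mean entered in its place can fall before that time, and it adds an apparent observation that carries no information. A carried-forward time, if it is the last recorded one, states that the event happened when observation stopped.

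Section 10.3 reaches these outcomes by its own terms. It covers follow-up data, section 9.2 puts the event times there, and the sensitivity analysis for the primary outcomes makes sense only if primary values have been filled in. The t-test, Mann–Whitney and Hodges–Lehmann comparisons need a value for every infant they include. The Kaplan–Meier and log-rank analysis does not, but section 10.3 does not keep imputed times out of it.

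At stake are the p-values, confidence intervals and effect estimates for both primary outcomes.

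**Working it through.** **Inputs.** From section 11: two-group comparison, α = 0.05, β = 0.2, SD 2 days, 1:1 allocation, 20% loss allowance, differences of 1.4, 1.2 and 1.2 days. From section 14.6: two-sided testing. Assumed, because the protocol does not say: whether the mean is by arm or pooled, the actual loss on each outcome, what is carried forward, and the mean event times.

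**The plan's own figures.** n per arm = 2(1.960 + 0.842)² × 2² / δ².
- δ = 1.4 gives 32.04 per arm, total 64 (66 if rounded up); stated 64.
- δ = 1.2 gives 43.6, so 44 per arm, total 88; stated 88.
- Dividing by 0.8 gives 80 and 110; stated 78 and 108, within 2.

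The inputs are therefore read correctly. The final strata correspond to 39, 54 and 54 infants per arm, 147 per arm overall.

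**Mean imputation by arm.** Let a fraction f of n infants per arm be filled with the arm mean.
- Filled values add nothing to the sum of squares, so the computed variance is about (1 − f)σ². The reported variance of the difference is about 2(1 − f)σ²/n.
- Only (1 − f)n values were observed, so the true variance is 2σ²/[(1 − f)n].
- The ratio of variances is (1 − f)², so reported SE / true SE ≈ 1 − f.
- Two-sided type I error ≈ 2[1 − Φ(1.96(1 − f))].

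| Loss f | SE ratio | Type I error |
|---|---|---|
| 5% | 0.95 | 6.3% |
| 10% | 0.90 | 7.8% |
| 20% | 0.80 | 11.7% |

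Simulation check (normal data, SD 2, 20% missing at random in each arm; 20,000 runs for the t-test, 3,000 for Mann–Whitney):

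| Per arm | Reported SE | True SE | t-test type I error | Mann–Whitney type I error |
|---|---|---|---|---|
| 39 | 0.400 | 0.508 | 11.8% | 18% |
| 54 | 0.342 | 0.432 | 12.1% | 19% |
| 147 | 0.209 | 0.259 | 11.3% | 24% |

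Coverage of the nominal 95% interval from the t-test was about 88%. Complete cases under the same random loss gave about 5% and 95%.

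**Mean imputation from the pooled data.** The difference becomes (1 − f) times the observed difference, and the reported SE shrinks by about the same factor. The test statistic is nearly unchanged: simulated type I error was 4.9%. The estimate is not: 0.8 × 1.2 = 0.96 days and 0.8 × 1.4 = 1.12 days at 20% loss. Simulated coverage of the true 1.2 or 1.4 days was 80–89%.

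**Carrying forward, read as last recorded time = event time.** Assume 54 per arm, SD 2 days, mean times of 5, 8 or 12 days, and loss spread evenly over the time before the event. A lost infant is then scored at about half the mean time, so with no true effect the false difference is about (difference in loss fraction) × mean/2.
- 8/54 lost on saline against 14/54 on milk (about 15% v 25%): 6/54 × 2.5, 4 or 6 = 0.28, 0.44 or 0.67 days in favour of milk (simulated 0.27, 0.44, 0.67).
- 5/54 against 16/54 (about 10% v 30%): 11/54 × 2.5, 4 or 6 = 0.51, 0.81 or 1.22 days. Simulated false-positive rates were 20–46%.
- Loss of 25% on saline and 15% on milk gives about the same sizes in favour of saline.
- Equal loss of 20% creates no false difference, but a true 1.2 days is estimated as about 1.06–1.08 days.

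**The planned sensitivity analysis.** Arm-mean filling leaves the difference in means exactly equal to the complete-case difference, so point estimates agree by construction. The intervals would differ, and a careful reader could see that. Section 10.3 does not say which result governs.

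**The case against.** The strongest reply is that section 10.3 fixes little. The two methods are examples, after a statement that the method will follow the mechanism. Section 9.2 also contains repeated measures such as weight and bilirubin, for which carrying forward has an ordinary meaning. Infants are followed daily (section 12.8), and the Kaplan–Meier analysis would handle non-informative loss correctly. The complete-case comparison offers a check.

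Part of this stands. A reader might draw four stronger conclusions that the documents do not support:
- That the trial will run at 11.7% type I error. This needs arm-specific means, which are not stated, and 20% loss on the outcome concerned. The 20% in section 11 is a sample-size allowance. Section 15 names withdrawal only between meconium evacuation and full feeding, so it points to the second primary outcome, not the first.
- That lost infants will be scored as early successes. Section 10.3 does not say what is carried forward for a once-only time. This is the natural reading, but it is an inference.
- That the bias favours breast milk. Nothing says which arm would lose more infants.
- That the sensitivity analysis is useless. It can show a changed interval, and complete cases are valid if loss is non-informative.

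What does not stand is that the rule is harmless. The named methods are stated as ones that will be used, no alternative is given, and the primary event times are within reach. The mechanism cannot settle the choice either: data can contradict missing completely at random, but cannot separate missing at random from missing not at random. Nor is this a detail left to an analysis plan, since the protocol itself names the unsuitable methods.

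**Conclusion.** The point holds in this form: section 10.3 names, as its only examples, two methods unsuited to a right-censored time, and leaves both primary outcomes open to them. The size is conditional:
- **Arm-specific means:** SE too small by about the loss fraction. Type I error is 6.3–11.7% over 5–20% loss with the t-test, and 18–24% at 20% loss with Mann–Whitney.
- **Pooled mean:** type I error near 5%, effect shrunk by the loss fraction, interval coverage below nominal.
- **Carried-forward last time:** bias only as large as the assumed event times and the imbalance in loss make it.

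These figures assume normal data and, for mean imputation, random loss. Real loss may be informative. In-hospital death is a listed adverse event (section 8.2), and section 7.3 gives sepsis and NEC among the reasons for termination. If that applies to the single infant, which is my reading, those whose feeding times go missing may be the sicker ones, and complete cases would be biased as well.

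**What to change.** In section 10.3, delete mean imputation and last observation carried forward for the two primary outcomes. In section 14.2:
- Make the Kaplan–Meier and log-rank analysis already planned the governing one. Include every randomised infant, censor at the last time known event-free, and let no imputed event time enter.
- Label the t-test, Mann–Whitney and Hodges–Lehmann comparison as supportive, on observed times only.
- Because death or termination for events such as NEC or sepsis may make censoring informative, add a sensitivity analysis that shifts lost infants' event times later by a range of days, separately by arm, and report where the conclusion changes. For a death, the limit of that shift is an infant who never reaches the event.

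The cost is wording, a little programming and possibly wider intervals. No new data are needed, because daily follow-up already gives the last event-free time.
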